## Abstract

**Background:**

The number of people with cardiovascular disease (CVD) and diabetes mellitus type 2 (T2DM) is growing rapidly. To a large extend, this increase is due to lifestyle-dependent risk factors, such as overweight, reduced physical activity, and an unhealthy diet. Changing these risk factors has the potential to postpone or prevent the development of T2DM and CVD. It is hypothesized that a cognitive behavioral program (CBP), focused in particular on motivation and self-management in persons who are at high risk for CVD and/or T2DM, will improve their lifestyle behavior and, as a result, will reduce their risk of developing T2DM and CVD.

**Methods:**

12,000 inhabitants, 30-50 years of age living in several municipalities in the semi-rural region of West-Friesland will receive an invitation from their general practitioner (n = 13) to measure their own waist circumference with a tape measure. People with abdominal obesity (male waist ≥ 102 cm, female waist ≥ 88 cm) will be invited to participate in the second step of the screening which includes blood pressure, a blood sample and anthropometric measurements. T2DM and CVD risk scores will then be calculated according to the ARIC and the SCORE formulae, respectively. People with a score that indicates a high risk of developing T2DM and/or CVD will then be randomly assigned to the intervention group (n = 300) or the control group (n = 300).

Participants in the intervention group will follow a CBP aimed at modifying their dietary behavior, physical activity, and smoking behavior. The counseling methods that will be used are *motivational interviewing *(MI) and *problem solving treatment *(PST), which focus in particular on intrinsic motivation for change and self-management of problems of the participants. The CBP will be provided by trained nurse practitioners in the participant's general practice, and will consists of a maximum of six individual sessions of 30 minutes, followed by 3-monthly booster sessions by phone. Participants in the control group will receive brochures containing health guidelines regarding physical activity and diet, and how to stop smoking. The primary outcome measures will be changes in T2DM and CVD risk scores. Secondary outcome measures will be changes in lifestyle behavior and cost-effectiveness and cost-utility ratios. All relevant direct and indirect costs will be measured, and there will be a follow-up of 24 months.

**Discussion:**

Changing behaviors is difficult, requires time, considerable effort and motivation. Combining the two counseling methods MI and PST, followed by booster sessions may result in sustained behavioral change.

**Trial registration:**

Current Controlled Trials ISRCTN59358434

## Background

Partly because of the ageing population, and partly due to changes in lifestyle and the resulting epidemic of obesity, there is an increasing percentage of people with diabetes mellitus type 2 (T2DM) and cardiovascular diseases (CVDs) in the general population. With a prevalence of 475,000 patients with diabetes and 65,000 new cases each year, diabetes mellitus is one of the most widespread chronic diseases in the Netherlands [1]. CVD is a major cause of disability and mortality in Western countries, and is responsible for one fifth of all disability-adjusted life years [2].

To a large extend, T2DM and CVD are caused by lifestyle dependent risk factors, such as overweight, reduced physical activity, smoking and an unhealthy diet [3-5]. Changing these risk factors has the potential to postpone or prevent the development of T2DM and CVD.

People who are overweight or obese often have a cluster of risk factors for T2DM and CVD, and the risk increases progressively as their body mass index (BMI) increases [6]. Apart from overall obesity, fat distribution is an important risk factor for T2DM and CVD [7]. Waist circumference reflects the magnitude of abdominal adipose tissue deposits as well as total fat mass, and thereby complements BMI in the evaluation of obesity-associated T2DM and CVD risk [8,9]. It is considered to be a good measure with which to identify persons with an increased risk of developing T2DM and CVD [10-12].

The Diabetes Prevention Program Research Group have shown that intensive lifestyle interventions that encourage people to achieve and maintain weight-loss are effective in lowering the incidence of T2DM [13]. In the Finnish Diabetes Prevention Study, a lifestyle intervention in middle-aged, overweight persons resulted in a 58% reduction or postponement of the overall incidence of diabetes [14]. A Dutch RCT showed that a lifestyle-intervention program according to general recommendations (i.e. regular dietary advice, and stimulation to lose weight and to increase physical activity) was effective and induced beneficial changes in lifestyle, which improved glucose tolerance in subjects with impaired glucose tolerance [15].

A wide variation of lifestyle interventions are reported in the literature. Components of interventions that have been found to be effective are: goal-setting [16], programs specifically tailored to the participants [14,17], the use of written materials [14,18], and continued subject-therapist contact, whether in person or by telephone, mail or e-mail [19]. Furthermore, effective interventions included those based on behavioral or cognitive-behavioral strategies, as opposed to health education or instruction alone [18-21].

### Theoretical background

A theory that has been proven useful for the development of behavioral interventions is the theory of planned behavior (TPB) [22,23]. The TPB helps us to understand how energy balance-related behavior is mediated by cognitive constructs [24]. According to the TPB, human action is guided by three kinds of considerations: a) behavioral beliefs: beliefs about the likely consequences of the behavior and the evaluation of these consequences; b) normative beliefs: beliefs about the normative expectations of others and the motivation to comply with these expectations; c) control beliefs: beliefs about the presence of factors that may facilitate, or may impede the performance of the behavior, and the perceived power of these factors. These beliefs can lead, respectively, to a favorable or an unfavorable attitude towards a certain behavior, perceived social pressure, and perceived behavioral control, and in combination they determine behavioral intention. Finally, given a sufficient degree of actual control over the behavior, people are expected to carry out their intentions when the opportunity arises.

Leventhal's theory of self-regulation proposes that individuals construct schematic representations of illness and health-threatening conditions according to the concrete and abstract sources of information that are available to them [25]. The theory starts with the premise that individuals are active problem-solvers. They make sense of a threat to their health by developing their own cognitive representations of the threat, which, in turn, determine how they respond. Health professionals such as nurse practitioners can be sources of information. The theory also assumes that a discrepancy between a person's goal or expected outcome and what exists (the actual situation) will motivate the person to take action and to reduce this ambivalence. Feedback on the discrepancy motivates a person to become actively engaged by attending to stimuli and making efforts to find a way to overcome the discrepancy between what is expected or desired and the present state [26].

### Cognitive behavioral program

The cognitive behavioral program (CBP) applies several components of both the TPB and the theory of self-regulation: The counseling techniques that are used in the intervention are motivational interviewing (MI) and problem-solving treatment (PST). MI aims to reinforce the attitude and the behavioral intention according to the TPB, and induces the ambivalence described in the theory of self-regulation. PST will be used to support the participant in finding ways to overcome this discrepancy. A further aim of the PST is to strengthen the participant's perceived behavioral control and to provide the tools to overcome barriers that hinder a structural change in lifestyle behavior.

MI is a client-centered counseling method with which to elicit behavioral change by helping people to explore and resolve ambivalence in a respectful counseling atmosphere [27]. It is a well-known method of counseling, and is considered to be a useful intervention strategy in the treatment of lifestyle problems [28]. The therapeutic relationship is more like a partnership or companionship than a setting with expert/recipient roles. Motivation is an integral part of changing an individual's behavior and stimulating the adaptation to good healthy habits. The four guiding principles of MI are: express empathy, develop discrepancies, roll with resistance, and support self-efficacy. MI may be a suitable counseling technique with which to establish personal relevance and awareness, so that a positive attitude towards behavioral change is likely to occur.

PST is a brief, structured psychological intervention, and can be defined as the self-directed cognitive-behavioral process by which a person attempts to identify or discover effective or adaptive solutions for specific problems encountered in everyday life [29]. The effects of PST have been proven to be effective in patients with depression [30,31]. PST may increase a person's ability to solve problems in a structured way and also result in increasing the person's self-management. The treatment involves an active collaboration between participant and therapist, with the participant taking an increasingly active role in planning the treatment and implementing activities between the treatment sessions. The therapist helps participants to gain a sense of mastery over their difficulties. Therefore, PST may be a valuable counseling method. The treatment can be provided by nurse practitioners, is relatively brief (i.e. only three to six 30-minute sessions are needed), and is therefore suitable for primary care.

### Objectives

The aim of the study is to investigate the effects of a CBP, compared with providing written information and brochures only. Primary outcomes are the absolute cardiovascular risk and risk of developing T2DM in people who are at high risk for T2DM and/or CVD. Secondary outcomes are changes in dietary behavior, physical activity, and smoking behavior in people who are at high risk for T2DM and/or CVD.

The cost-effectiveness and cost-utility ratios will also be assessed.

## Methods

### Design of the study

The study is designed as a multicenter randomized controlled trial with a two-year follow-up and an economic evaluation alongside. Participants will be recruited through a two-step screening procedure (Figure 1), and those who are eligible and consent will be randomly assigned to the intervention group or the control group. The Medical Ethics Committee of the VU University Medical Center in Amsterdam approved the study design, protocols, information letters and informed consent form.

**Figure 1 F1:**
[figure not shown]
Design of the RCT

### Setting

The trial will be conducted in the Diabetes Research Center in Hoorn, in the Netherlands. The intervention will be provided by nurse practitioners in 12 general practices in several municipalities in the semi-rural region (West-Friesland) surrounding the city of Hoorn.

### Study population

Twelve thousand inhabitants (men and women) aged 30-50 living in this region will be invited to participate in a selective screening procedure. The target group will be approached, after identification of date of birth and absence of diabetes or known CVD, from participating general practices (n = 12).

In the first step of the screening procedure the inhabitants will receive an invitation to measure their own waist circumference with a tape measure, according to detailed instructions. Waist circumference is a widely used indicator of abdominal obesity in population studies. To minimize non-response we will use the modified Tailored Design Method [32] to approach potential participants. The main elements of this approach are: a brief pre-notice postcard is sent to each of the sampled persons, and a few days later a comprehensive and easy to understand invitation is sent, together with the tape measure and a stamped addressed envelope for the reply. A week after this mailing, another postcard will be sent, in which the respondents are thanked for returning the survey questions and the non-respondents are asked to complete the waist-measurement and return it immediately. Four weeks later, a reminder and a replacement tape measure are sent to the non-respondents. Abdominal obesity is, in principle, defined as a waist circumference of 88 cm or more for women, and 102 cm or more for men [33]. All respondents with a waist circumference of 1 cm under this cut-off point or above will be invited to participate in the second step of the screening at the research center. After signing an informed consent form, this screening will include the measurement of blood pressure, a blood sample (to determine total and HDL cholesterol, triglycerides, fasting plasma glucose, HbA1c), and anthropometric measurements (height, weight, and waist and hip circumference). In addition, the participants will be given a questionnaire to fill in at home, including questionnaires about physical activity, dietary intake, smoking status, determinants of behavior according to the TPB, quality of life, and depression.

The 9-year risk of developing diabetes will be estimated using the risk function derived from data of the Atherosclerosis Risk In Communities (ARIC) Study [34], with ethnicity (black yes/no), parental history of diabetes, systolic blood pressure, waist circumference and height (Additional file 1).

The 10-year risk of a fatal cardiovascular disease will be estimated using the formulae developed by the Systematic COronary Risk Evaluation (SCORE) project [35], with gender, smoking status, total cholesterol and systolic blood pressure (Additional file 2, see Tables 1 &2).

**Table 1 T1:** Coefficients for Eq. (1)

		CHD		Non-CHD	CVD
				
		α	p	α	p
Low risk	Men	-22.1	4.71	-26.7	5.64
	Women	-29.8	6.36	-31.0	6.62
High risk	Men	-21.0	4.62	-25.7	5.47
	Women	-28.7	6.23	-30.0	6.42

**Table 2 T2:** Coefficients for Eq. (2)

	CHD	Non-CHD
Current smoker	0.71	0.63
Cholesterol (mmol/L)	0.24	0.02
Systolic BP (mmHg)	0.018	0.022

For both scores and for each participant, age will be extrapolated to 60 years to address the problem of a high relative but low absolute risk in younger persons. This way it is possible to flag persons who will become at high absolute risk [36].

All participants with a minimum risk of 10% for developing diabetes and/or a minimum risk of 10% for CVD will be randomly assigned to either the intervention group or the control group. Exclusion criteria are: inability to communicate adequately in the Dutch language and pregnancy.

### Treatment allocation

An allocation schedule will be drawn up with a computerized random number generator. If there is more than one participant from a family, the consecutive members of that family will be allocated to the same group to avoid contamination. Randomization will be performed by an independent administrative assistant from the Diabetes Research Center, who is not involved in the intervention.

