### Blinding

It is impossible to blind the participants and nurse practitioners for the intervention, but the research assistants, the principal investigator and the GPs will remain blinded during the entire intervention. This is achieved by instructing the participants not to communicate about the intervention with their GP or the medical assistants.

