### Study duration

The counseling sessions will last for 2-4 months, and the total intervention period, including booster calls, will be 16 months. Together with an estimated inclusion period of 8 months, the study itself will take 24 months (2 years). The measurements will be carried out before the start of the intervention, and after 6, 12 and 24 months. The baseline measurements started on February 14^th^, 2008.

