### Sample size

In a Dutch working population of overweight people (BMI ≥ 25), which consisted of both males and females, the standard deviation of the ARIC score was found to be 8.11 [45]. For a two-sided detection of a 5% between-group difference in cardiovascular risk score, standardized at 60 years of age, with an alpha of 0.05 and a power of 90%, in the present study 120 participants will be needed in the intervention group and 120 in the control group. Assuming that 40 participants per collaborating GP are recruited, and each participant is randomized independently, this is feasible. We expect a response of approximately 65% in the first step of the screening, 20% of which will meet the abdominal obesity criterion [46,47]. Of those who meet this criterion, we expect that at least 80% will be willing to participate in the second step and the RCT (Figure 1).

A multilevel analysis is performed to be able to adjust for the clustering of observations within practices. To be able to perform stratified and multivariable analyses, and taking loss to follow-up into account, larger numbers will be needed. A total of 600 (i.e. 300 in the intervention group and 300 in the control group) is expected to suffice.

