### Analyses

Descriptive statistics (means ± SD, or median and interquartile ranges, as appropriate) will be used to describe the entire study sample with regard to demographics, physical measurements and baseline lab values. The analyses will be conducted according to the intention to treat principle. Multilevel analyses will be performed to adjust for the clustering of observations of participants receiving care from the same nurse practitioner, and for repeated measurements within one patient. Linear and logistic regression models will be used to examine the effect of the intervention on each of the outcome measurements. Differences in changes between groups will be calculated with 95% confidence intervals. If there are any relevant differences in baseline measurements between the two groups, we will adjust the outcome for these factors (i.e. age, gender, ethnicity, BMI at the start of study, level of education, depression, smoking, number of sessions attended). Separate analyses of effect modifiers (i.e. gender, age) will be performed in order to gain a better understanding as to who benefits most from the intervention. Separate analyses of effect modifiers and mediators will be conducted in order to gain a better understanding as to who benefits most from the intervention

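### Relatives are allocated together, which contradicts the statement that each participant is randomised independently, and the listed clustering levels leave out the family

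*Protocol article*

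**What the plan says.** All references are to the protocol article.

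- *Treatment allocation*: the schedule comes from a computerised random number generator and is run by an independent administrative assistant. For families with more than one participant, "the consecutive members of that family will be allocated to the same group to avoid contamination".
- *Sample size*: after giving 120 per arm, the text assumes 40 recruits per collaborating GP and that "each participant is randomized independently, this is feasible". It continues: "A multilevel analysis is performed to be able to adjust for the clustering of observations within practices".
- *Analyses*: multilevel models will "adjust for the clustering of observations of participants receiving care from the same nurse practitioner, and for repeated measurements within one patient".
- *Blinding*: "It is impossible to blind the participants and nurse practitioners for the intervention". Participants are told not to discuss the intervention with their GP or the medical assistants; relatives are not mentioned.
- *Study duration*: recruitment is spread over an "estimated inclusion period of 8 months".

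**The concern.** Two statements about the unit of allocation cannot both be true. If a second family member takes the arm of the first, that second member is not randomised independently.

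The analysis then leaves out the level that this rule creates. The article does list its clustering levels, so this is not simply a detail left to another document. The practice or nurse level does not stand in for the family. Participants are otherwise allocated individually, so both arms will normally occur within a practice, and a shared practice effect largely cancels in the comparison of arms. A family lies wholly in one arm, so its shared effect does not cancel. The reason given for the rule, contamination, itself presumes that relatives influence each other's behaviour. What is at stake is the stated precision: intervals somewhat too narrow and a type I error somewhat above 5%.

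A second, less certain, issue is selection. Where relatives enter one after another, the later one's arm is fixed before they enrol and may be known to them.

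**Working it through.** **The plan's own figure.** With a difference of 5 (reading the stated 5% as 5 points), SD 8.11, two-sided alpha 0.05 and 90% power, n per arm = 2 × (1.960 + 1.282)² × 8.11² / 5² ≈ 55.3, so 56 (57 by the t-test). The stated 120 does not reproduce. That is a separate matter, and nothing below depends on it.

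**Formula.** Let f be the share of participants who belong to a same-arm family pair and r the within-pair correlation of the analysed outcome. Each paired participant adds one covariance term, so the variance of an arm mean is (σ²/n)(1 + f·r).

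- Design effect: DE = 1 + f·r
- Ratio of true to reported standard error: √DE
- True two-sided alpha at nominal 0.05: 2 × [1 − Φ(1.96/√DE)]
- Effective size of 300 per arm: 300/DE

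**Inputs.** The documents give neither f nor r. Assumed ranges: f = 0.05–0.30, r = 0.1–0.5.

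| f | r | DE | √DE | true alpha | effective n of 300 |
|---|---|---|---|---|---|
| 0.05 | 0.1 | 1.005 | 1.002 | 0.0506 | 298.5 |
| 0.10 | 0.1 | 1.010 | 1.005 | 0.0511 | 297.0 |
| 0.10 | 0.5 | 1.050 | 1.025 | 0.0558 | 285.7 |
| 0.20 | 0.3 | 1.060 | 1.030 | 0.0570 | 283.0 |
| 0.30 | 0.3 | 1.090 | 1.044 | 0.0605 | 275.2 |
| 0.30 | 0.5 | 1.150 | 1.072 | 0.0676 | 260.9 |

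**Where f is likely to lie.** The recruitment figures allow a rough check. They give the chance that one invited relative of a randomised person is also randomised:

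- No concordance within families: 600/12,000 = 5%.
- Response to the invitation (65%) fully shared: 0.05/0.65 = 7.7%.
- Willingness to continue (80%) also fully shared: 0.05/(0.65 × 0.80) = 9.6%.

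If each participant had one invited relative, f would be about 5–10%. Reaching 20–30% would need the relative's chance of meeting the waist and risk criteria to be about two to three times that of the average invitee (0.20/0.096 = 2.1; 0.30/0.096 = 3.1), or several invited relatives per participant. With f = 0.05–0.10, the design effect is 1.005–1.05 and the true alpha 0.051–0.056.

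**Power.** At the worst design effect, 120 per arm becomes 120 × 1.15 = 138, against 300 planned. With the stated difference of 5 and SD of 8.11, power at 260.9 effective per arm stays above 99.9%.

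**Knowledge of allocation.** Four features bear on this: relatives follow in sequence, recruitment lasts months, participants are unblinded, and the instruction on silence does not cover relatives. An independent assistant cannot conceal an arm already set by rule. Each individual consents before the second-step measurements, but the text does not say that all eligible relatives do so before the family's allocation is opened.

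**The case against.** The strongest reply is that same-arm allocation is a sensible and openly stated guard against contamination, and that its numerical effect is small. That stands: the rule itself need not change.

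Several stronger readings are tempting, and the documents do not support them:

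- *That 120 per arm was derived from independent randomisation.* The independence clause comes after that figure and concerns whether recruitment is feasible; it probably means individual rather than practice-level randomisation. It is still wrong for families and easily corrected.
- *That concealment fails for every second and later relative.* The text does not say that relatives join after an arm is disclosed. Those allocated at the same time are unaffected, and the number who enter later is unknown.
- *That standard errors are at least 2% too small.* This needs a sizeable share of participants in pairs. The recruitment figures point to less unless waist and risk cluster strongly in families.
- *That parental diabetes, a term in the ARIC score, drives the correlation.* Siblings share it but spouses do not, and it is fixed over time, so it adds little to correlation in change scores.
- *That the trial is underpowered.* The planned 600 absorbs the loss.

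It can also be said that bootstrap details and sensitivity analyses belong in an analysis plan. That is fair for those items. It does not excuse a list of clustering levels that omits the one created by the allocation rule.

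**Conclusion.** The contradiction over the unit of allocation and the missing family level both hold. Under the assumed ranges, the design effect is 1.005–1.15, the standard error about 0.25–7% too small and the true alpha about 0.051–0.068. These figures assume families of two; larger families would raise them. The low end is the more plausible, so this is a modest flaw in stated precision, not a threat to power.

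The possibility that later relatives choose participation knowing their arm is an inference from sequential entry and lack of blinding. It is limited to those who enter after the first member's arm is known. Its size cannot be estimated from the documents, but a larger sample would not remove it.

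**What to change.** 1. In *Sample size*, replace the independence statement: participants are randomised individually, except that members of one family are allocated together as a unit.
2. In *Analyses*, add a family random effect, or standard errors robust to clustering by family, to the linear and logistic models. In *Economical evaluation*, resample whole families in the bootstrap.
3. Add a sensitivity analysis limited to the first-randomised member of each family. It removes both the clustering and any selective entry of later relatives.
4. Where several eligible members are known at screening, complete consent and baseline for all of them before opening the family's allocation.

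The cost is low, because the allocation rule already requires families to be identified. The added level will be sparse, since most families will have one participant, so a random effect may be poorly estimated; robust errors are then the simpler choice. Intervals will be slightly wider, and step 4 may delay some allocations.
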